#### Additional Analyses

In additional analyses, using the intent-to-treat sample and the baseline (week 0), mid- (week 4) and post- (week 8) active-treatment (randomized) phase values for continuous clinical variables (GDS, BAI, BDI, SF-36, patient ratings, functional status indicators), we will use random regression models (RRM) analyses (or equivalently, hierarchical linear model [HLM] or mixed effects models) to compare the Telepsychology and Same-Room conditions over the 8-week active phase time tracjectory. These analyses will use scores for each outcome as the dependent variable and delivery mode (treatment) and time (time by treatment) as the primary independent variables. The random regression approach estimates individual change in outcome for each subject in addition to estimating average change in outcome within each treatment population. Specifically, random regression models allow for measurement of subjects at different time points, missing data, and time varying or invariant covariates [68-74]. Further, longitudinal methods for binary outcomes [75-77] will be used to compare the Telepsychology and Same-Room conditions for the dichotomous outcome measure (MDD response status measured at weeks 4 and 8). Methods for categorical or ordinal outcomes [78-82] will also be applied where appropriate.

Exploratory multivariable logistic regression, assuming drop-outs are nonresponders, will be used to determine the set of predictor variables associated with treatment response (dichotomous outcome: treatment responder/nonresponder as described under primary analyses). In additional exploratory analyses, RRM analysis will be used to evaluate the effect of putative confounding or prognostic variables on continuous or binary clinical outcomes following the 8-week treatment course, and the possible effect modification (interaction) of these variables on the relationship between treatment status (delivery mode) and clinical outcome. Interaction between treatment status variables and covariates will be evaluated by inclusion of treatment by covariate interaction terms in the model. In a final set of analyses, we will compare the single end of study measure (change from baseline) for the outcome variable using a multivariable regression approach with treatment status as the primary independent variable, with missing values imputed using the method of Little and Rubin [83]. Analyses will be repeated for each of the clinical measures, both with and without a Bonferroni correction [84] for the multiple outcome variables. In other words, both the unadjusted and Bonferroni-corrected p-values will be obtained to evaluate sensitivity of conclusions to the "multiple comparisons" effect.

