### Sample Size Determination and Power Analysis

The primary response variable for sample size calculation is the proportion (%) of patients who respond to treatment. Treatment response is defined as at least a 50% improvement from baseline to post-treatment level on the GDS [percent change from baseline: (baseline-post)/baseline ≥ 50%]. Demonstration of non-inferiority among treatments differs from that of establishing superiority. For a non-inferiority trial, the null hypothesis states that two treatments are non-equivalent, that is they differ by at least a clinically relevant amount, Δ. [55-62]. The approach will be formulated in terms of the one-sided non-inferiority problem [55,60,61,63] because it is of interest only to test that the treatment response (% responders) for the Telepsychology mode of delivery is not too low compared to that for the standard Same-Room mode of delivery. Note that, for non-inferiority trials, the consequence of a false positive (ie, claiming the novel therapy [Telepsychology] is worse than the standard therapy [Same-Room] when it is, in fact, non-inferior) is to keep patients on the standard therapy. Therefore, the Type I error rate, α, can be set higher than in traditional superiority trials (eg 0.1–0.2) [64].

We estimate that the % treatment responder for Same-Room delivery (P) is 0.70. We assume that a maximum clinically unimportant difference in response proportion (Δ, the non-inferiority effect size) is 0.15 between Telepsychology and the standard Same-Room service delivery (upper limit of one-sided 90% confidence interval must not be greater than Δ = 0.15 for the conditions to be declared equivalent). Using the tables of Machin and Campbell [64] and assuming Δ = 0.15, one-sided α = 0.10, P = 0.70, and power = 0.85, we estimate that approximately n_1 _= n_2 _= 100 subjects per condition are needed for overall treatment effects comparisons. If we further assume that 10% of subjects will not have at least one post baseline measurement (i.e. will not be included in the ITT sample), then 112 subjects must be randomized to each treatment group to yield the required sample size for the primary intent-to-treat analyses (n_1 _= n_2 _= 100/group).

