For the ITT sample (n_1 _= n_2 _= 100/treatment group) we will be able to estimate the individual (main effects) end of treatment means for each of the continuous clinical and process measures with a precision of ± 0.2 standard deviations. For the primary outcome measure Δ_Δ1 _= Δ_(Post)T_- Δ_(Post)S_, which measures the difference in change from baseline (pre to immediate post treatment) for the continuous outcome domain measures for the telepsychology condition compared to change from baseline for the standard (same-room) condition, we will be able to estimate with a precision of ± 0.3 standard deviation units using 95% confidence intervals for the difference in two means (Δ_(Post)T_, Δ_(Post)S_), where the appropriate standard deviation is the pooled standard deviation for comparing change from baseline for the telepsychology condition versus the standard condition.

Assuming that 20% of subjects will drop out of the ITT sample (n_1 _= n_2 _= 80, assuming equal treatment distribution of dropouts), we will be able to estimate for the completer sample the individual end of treatment means for each of the measures with a precision of ± 0.2 standard deviations, and the difference in change from baseline (pre to immediate post treatment) for the outcome domain measures with a precision of ± 0.3 standard deviation units.

Both the standard deviation and the distribution of costs are presently unknown for the type of patients who will be enrolled in Telepsychology. Thus, it is difficult to obtain a meaningful estimate of the power to detect a difference in CE from any arbitrary value. We propose to determine costs and apply to our economic model after the completion of the study, and then use the bootstrap technique to obtain a 90% Confidence Interval (CI) around the estimated costs. The bootstrap technique is appropriate because, as noted, the distribution of costs for these types of patients is presently unknown.

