In addition to comparing unadjusted % responders between the modes of delivery conditions, it also is of interest to compare % responders, adjusted for putative confounding variables. Possible covariables to be considered for inclusion in these analyses include initial disease severity as measured by baseline GDS or BDI score, use of psychiatric medication, number of other co-morbid conditions, and relevant others as identified though the preliminary descriptive analyses. Two approaches will be used to evaluate non-inferiority of adjusted % responders for the two delivery conditions. The method of Gart and Nam [65] and Nam [59], which involves calculation of a non-inferiority test statistic within strata of potential confounding variables, formulates a score test for a null hypothesis of a common specified clinically relevant non-zero difference in % responders between two treatments for multiple 2 × 2 tables. Because the above procedure may be limited by the number of covariables (number of strata) that can be used, we will carry out a second set of analyses using a multivariable logistic regression model to obtain estimates of adjusted % responding for each treatment delivery condition for a specified set of values for the covariables, and then will apply the methods described above (one-sided confidence intervals and non-inferiority hypothesis testing) to evaluate non-inferiority of the two interventions. The response variable for these analyses is the dichotomous outcome, responder/non-responder to treatment, with missing data from premature exits treated as non-responders. The primary independent variable is treatment condition.

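### The exploratory predictor model codes every drop-out as a non-responder, so it models staying and responding, and correlates of leaving can be misread as predictors of poor response

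*Protocol article*

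**What the plan says.** The Additional Analyses section of the protocol article sets the rule: "Exploratory multivariable logistic regression, assuming drop-outs are nonresponders, will be used to determine the set of predictor variables associated with treatment response". The outcome is the responder classification of the primary analysis. The Primary Clinical Outcome section uses the same rule when it compares adjusted response between the two delivery modes, "with missing data from premature exits treated as non-responders". For the predictor model the article names no version with observed or imputed response, and no companion model for drop-out.

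The same paragraph of Additional Analyses plans two neighbouring analyses:
- random regression models that examine prognostic variables and treatment-by-covariate interactions;
- a regression comparison of the treatments on change from baseline, "with missing values imputed using the method of Little and Rubin".

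The planning figures are in Sample Size Determination and Power Analysis: "We estimate that the % treatment responder for Same-Room delivery (P) is 0.70" and "Assuming that 20% of subjects will drop out of the ITT sample". The Abstract and the Study Aims list drop-out among the process variables, apart from the clinical outcomes.

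**The concern.** Counting drop-outs as failures is a recognised convention when two arms are compared. The predictor model asks a different question: which features distinguish patients who improve from those who do not. With drop-outs placed among the non-responders, two events share one code, leaving and not improving. A feature that makes patients leave, but has no bearing on whether the therapy works, then acquires an association with the coded outcome.

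The article's Rationale describes older adults with mobility, transport and isolation problems, and number of comorbid conditions is a named candidate covariate. Such features could plausibly affect attendance. If they were reported as predictors of poor response to Behavioral Activation, the reader would be told something about the therapy that is really about retention.

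**Working it through.** **Inputs from the article (Sample Size Determination and Power Analysis).** Expected Same-Room response 0.70; margin 0.15; one-sided α 0.10; power 0.85; 10% with no post-baseline measurement; 112 randomised per arm; 100 per arm in the intention-to-treat sample; a further 20% drop-out, leaving 80 completers per arm. The 0.70 is applied to both arms, as the non-inferiority calculation implies.

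**The plan's own figure.** The inputs are "assuming Δ = 0.15, one-sided α = 0.10, P = 0.70, and power = 0.85".
- n per arm = 2 × 0.70 × 0.30 × (1.2816 + 1.0364)² / 0.15² = 100.3, against about 100 stated. Power at 100 per arm is 0.849.
- 100 / 0.90 = 111.1, rounded up to 112, as stated.

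The planning figures are therefore coherent and can be carried forward.

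**Share of coded non-responders who lack the endpoint.** Let d be the drop-out proportion. The article does not say whether 0.70 is the rate among completers or the rate after drop-outs are counted as failures, so both readings are shown.
- Completers: share = d / [d + 0.30(1 − d)]. With 200 patients, 40 drop out and 0.30 × 160 = 48 completers do not respond: 40/88 = 45%.
- Drop-outs already counted: share = d / 0.30. Coded non-responders are 0.30 × 200 = 60: 40/60 = 67%. This reading implies 140/160 = 87.5% response among completers.

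**Sensitivity to drop-out (200 patients).**

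| Drop-out | 70% among completers | 70% after coding |
|---|---|---|
| 10% | 27% | 33% |
| 15% | 37% | 50% |
| 20% | 45% | 67% |
| 25% | 53% | 83% |

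The Randomization section puts every randomised patient in the intention-to-treat analysis. If all 224 are analysed, the 24 without any post-baseline value join the 40. The shares become 64/112 = 57% and 64/67.2 = 95%.

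**Mechanism (assumed example).** Take a binary covariate split 50/50 and unrelated to response, with drop-out of 10% at one level and 30% at the other (mean 20%).
- Completer response 0.70: coded non-response is 0.10 + 0.90 × 0.30 = 0.37 against 0.30 + 0.70 × 0.30 = 0.51. The odds ratio is (0.51/0.49)/(0.37/0.63) = 1.77.
- Completer response 0.875: 0.10 + 0.90 × 0.125 = 0.2125 against 0.30 + 0.70 × 0.125 = 0.3875. The odds ratio is 2.34.

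The true odds ratio for response is 1.0 in both cases. With 100 patients per level, the chance of p < 0.05 is about 51% and 76%.

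**Simulation (assumed covariate effects).** 3,000 trials of 200 patients, mean drop-out 20%, drop-out logistic in a covariate that does not affect response. The article gives no covariate effect on drop-out, so the odds ratios are assumptions.

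| Drop-out odds ratio per SD | Flagged, completer response 0.70 | Flagged, completer response 0.875 |
|---|---|---|
| 1.5 | 23% | 40% |
| 2 | 53% | 79% |

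Observed responses alone flag it in 4% to 5%. That is expected by construction, because drop-out here depends only on the covariate.

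**What an observed-only fit would leave.** 48 non-responders among 160 completers on the first reading, 160 − 140 = 20 on the second.

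**The case against.** The strongest reply has four parts.

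1. The coding is openly stated and matches the primary endpoint, in a model labelled exploratory. On that view the model correctly predicts the trial's own composite. This stands as a reason to keep the model. It does not make the composite the same thing as response.

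2. The next sentence of the article plans random regression models for prognostic variables and interactions, and these do not need the coding. This also stands: the plan does not rest on the logistic model alone, and questions about who does better with which delivery mode belong to those interaction terms. It softens the consequence but does not correct the list of predictors that the logistic model will produce.

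3. The simulation sets up the one situation in which analysing observed responses is valid. Drop-out caused by poor response, which the planned coding guards against, was not simulated. This is fair. The simulation shows that the planned coding can mislead; it does not show that an observed-only fit is safe. With only 20 to 48 non-responders, such a fit is also thin for a multivariable model.

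4. Patients who drop out of the intention-to-treat sample, as the sample size section defines it, have at least one post-baseline measurement. So they lack the endpoint, but are not wholly unobserved. This is right, and it is a reason to prefer imputation that uses those scores.

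A reader might also infer that the plan already uses multiple imputation for this purpose. The text does not say so: it cites an imputation method without describing it, and for a different analysis, the treatment comparison of change scores.

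**Conclusion.** The point holds as a minor one. The article fixes a coding that turns a search for predictors of response into a model of completing and responding. On its own planning figures, 45% to 67% of coded non-responders in the sample of 200 would lack the endpoint. This rests on the 20% drop-out figure, which the article gives for completer precision around the end of treatment. Loss by the 12-month assessment could differ, and at 10% drop-out the share is 27% to 33%.

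Two stronger readings are not supported. One is that the model is bound to report predictors of leaving as predictors of response: this happens only for covariates related to drop-out, and the 23% to 79% range depends on assumed odds ratios of 1.5 to 2 per SD. The other is that the trial's main conclusion is at risk: this model plays no part in the primary non-inferiority comparison.

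**What to change.** Keep the planned model, but label its outcome 'completed and responded'. Add two models:

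- (a) The same predictor model with missing response multiply imputed from baseline and available post-baseline scores. This is preferable to an observed-only fit because of the small number of observed non-responders.
- (b) A separate logistic model for drop-out with the same candidate predictors.

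Name a variable as a predictor of response only if it holds in (a).

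The cost is two extra exploratory models and a few sentences of text. Model (a) assumes that response is missing at random given the scores used. The non-responder coding, kept alongside, shows one extreme alternative to that assumption; it does not test it.

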### Economic Analyses

A Markov-type economic model will be used to predict flow of funds and event rates over a 3-month and 12-month period for populations with depression based on outcomes and effectiveness data. The model will use actual event data reported by participants through survey at follow-up. The reason for including all costs is that it is sometimes difficult to distinguish depression-related from non-depression events. However, we will attempt to separate hospitalizations and office visits associated with a patient's depression problems from non-depression episodes of care. Another reason for including all costs is that depression is comorbid with many other conditions and the benefit of treatment may go beyond mental health costs. Thus, we will measure total cost savings and, based on patient response, separate depression-related costs from the cost offset. Capital costs will be annualized and depreciated over the life of the equipment, thus calculations for a 12-month period should be straightforward. Potential costs savings of Telepsychology will be based on sensitivity analysis of the fluctuations in the proportion of those appropriately treated with traditional Same-Room mental health care service delivery, compared to the actual proportion from those in the Telepsychology analysis.

Patient-oriented resource utilization data will be linked to participant's clinical data and a set of standard cost weights developed from archival VA billing data sources from patients with depression. The resources reported by the study participants (including medications) will be converted to dollar values using standard cost weights estimated from DSS administrative data. Average cost per day and average cost per admission will be calculated. Outpatient costs will include the average cost per clinic visit. Cost weights will be applied to the survey responses. To gain further insight into the variation in the resource utilization and costs of Telepsychology, sensitivity analyses will be performed. Sensitivity analysis involves systematically altering our assumptions about the costs and health effects of Telepsychology and noting the effect on the resulting cost/savings estimates. Two types of sensitivity analyses will be performed. The first set of calculations will be one-way sensitivity analyses. In one-way sensitivity analysis, the assumption about each parameter (eg, cost of telepsychology hardware) is varied over a reasonable range of values with all other parameters fixed. Finally, we will develop favorable and unfavorable scenarios for Telepsychology based on various assumptions including, but not limited to capital costs of telepsychology, technology "downtimes," and clinical outcomes. Because the specifics of these scenarios will depend on the nature of our findings, we cannot describe fully these analyses a priori. Nonetheless, these scenarios will reflect our understanding of the variation surrounding the cost estimates and the correlations among those parameters.

Cost data will be displayed in tables to highlight the extent to which costs cluster around videoconferencing technology, as well as patient-related utilization such as initial hospitalizations, outpatient visits, non-healthcare patient costs, medications and readmission(s). Costs will also be displayed graphically in a cumulative fashion, with cost on the horizontal axis and percent of patients with a specified or lower cost on the vertical axis. Finally costs will be displayed over time, with time on the x axis and mean cost on the y axis. Means and standard deviations of costs will be presented for each component of cost. "Trimmed" means and standard deviations of costs will be presented when 10% largest values and 10% smallest values are ignored. This way the summary statistics are less influenced by a small number of extreme outliers. Another possibility is to consider median as a measure of location and inter-quartile range as a measure of variance. However the usual or trimmed means and standard deviations seem more appropriate for this analysis because health care providers and payers may be concerned more about average cost, not median cost.

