### Study Aims & Objectives

The objective of the study is to test the hypothesis that in-home video-conferencing technology ("Telepsychology") will be as effective as the more traditional mode of service delivery ("Same-Room") for treating older adult veterans suffering from major depressive disorder (MDD). This objective will be accomplished by (1) Using an established, highly effective and well-tolerated behavioral treatment for depression (i.e. Behavioral Activation Treatment for Depression (BATD) [45-47]; (2) Employing a randomized between groups experimental design; (3) Examining standardized, repeated dependent measures of: (a) clinical outcomes, such as symptom severity, social functioning, and medical status; (b) process variables, such as patient satisfaction, treatment adherence, and treatment dropout rates; and (c) economic outcomes; and (4) conducting analyses to examine for outcome differences between African-American and Caucasian patients.

The primary research questions of the proposed study are:

1. Is in-home telepsychology for major depressive disorder in older adults as effective as same-room treatment on clinical and process outcomes?

2. Is in-home telepsychology for major depressive disorder in older adults cost-effective?

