**Resource Utilization Questionnaire **[89]	Previously validated questions on resource utilization will be administered as part of the baseline, 3-, and 12 month assessments. The questionnaires are 1 page long and capture information on hospitalizations, physician/professional visits, and medications. The baseline assessment will capture differences between groups and allow for the control of possible group variation during data analysis.

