#### Economic Outcome Measures

The economic analysis will determine the cost and potential cost savings of Telepsychology. Comprehensive information will be gathered on 1) telepsychology-related capital expenditures, and 2) patient-related resource utilization over 12 months for all patients in the project. This will allow us to estimate the combined spectrum of investment expenditures and direct in-hospital cost of Telepsychology as well as cumulative health costs over 12 months. In addition, a Markov-type economic model [54], determining transition probabilities between different health states, will be developed to predict flow of funds and event rates over a 12-month period for Telepsychology participants based on outcomes.

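### The economic plan never commits to a between-arm comparison of cost and response, and one promised cost category has no described source

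*Protocol article*

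**What the plan says.** All references are to the protocol article.

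- **Question.** Study Aims & Objectives lists as the second primary research question: "Is in-home telepsychology for major depressive disorder in older adults cost-effective".
- **Rule for savings.** Economic Analyses states: "Potential costs savings of Telepsychology will be based on sensitivity analysis of the fluctuations in the proportion of those appropriately treated with traditional Same-Room". The other side of that contrast is an observed figure: "compared to the actual proportion from those in the Telepsychology analysis".
- **Model population.** Economic Outcome Measures describes the Markov-type model as predicting costs and events for Telepsychology participants. Economic Analyses describes the same model as applying to people with depression in general.
- **Inference.** Sample Size Determination and Power Analysis says that the investigators will "use the bootstrap technique to obtain a 90% Confidence Interval (CI) around the estimated costs". It gives no cost standard deviation and no economic power.
- **Data.** Economic Outcome Measures plans to gather "patient-related resource utilization over 12 months for all patients in the project".
- **Cost categories.** Economic Analyses will tabulate "initial hospitalizations, outpatient visits, non-healthcare patient costs, medications and readmission(s" alongside technology costs. The Resource Utilization Questionnaire entry in Table 2 says that the forms "capture information on hospitalizations, physician/professional visits, and medications".
- **Summaries.** Economic Analyses presents ordinary means and standard deviations for each cost component. It adds that trimmed "means and standard deviations of costs will be presented when 10% largest values and 10% smallest values are ignored".

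**The concern.** Whether one mode of delivery is cost-effective relative to another is a question about two differences: in cost and in effect, between the randomised arms. The stated rule for savings is not of that form. One side is observed (Telepsychology) and the other is moved about in a sensitivity analysis (Same-Room). The quantity being moved, the proportion appropriately treated, is not defined anywhere and is not the responder proportion used for the clinical outcome.

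At stake is the protection that randomisation gives to the second primary question. If the Same-Room side is a range of chosen values, the savings estimate depends on that choice, and an interval around costs says nothing about the uncertainty of the difference.

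A second, smaller problem is that a cost category is announced for display with no described means of collecting it.

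**Working it through.** **1. Is there an economic figure to reproduce?** No. The article gives no cost mean, standard deviation, power or precision. The only input taken from its sample-size section is n = 100 per arm, which reproduces: 2 × 0.70 × 0.30 × (1.2816 + 1.0364)² / 0.15² = 100.3, and 100 / 0.90 = 111.1, rounded up to 112 randomised.

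**2. What each economic statement commits to.**

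| Element | What is stated | Between-arm? |
|---|---|---|
| Savings | Same-Room proportion varied, Telepsychology proportion observed | Not as a comparison of two observed arms |
| Markov model, Economic Outcome Measures | Telepsychology participants | No |
| Markov model, Economic Analyses | People with depression | Not stated |
| Bootstrap 90% interval | Estimated costs | Not stated |
| One-way sensitivity analyses and scenarios | Assumptions about Telepsychology costs and effects | No |

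No row names a cost difference, an incremental ratio or a net benefit between arms. The two descriptions of the model population disagree.

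**3. What the data would allow.** Resource use is collected at baseline, 3 months and 12 months in both arms. The baseline form is there so that group differences can be controlled. Utilisation is converted to dollars with standard cost weights and linked to each participant's clinical data. These are the ingredients of an adjusted between-arm analysis.

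**4. Why the target of the interval matters.** Let CV be the coefficient of variation of 12-month cost. It is assumed here, because the article says the cost distribution is unknown. Assume also the same mean and CV in both arms. As a fraction of mean cost, the half-width of a two-sided 90% interval is:

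- one arm's mean: 1.645 × CV / √n
- the between-arm difference: 1.645 × CV × √(2/n)

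| Assumed CV | One arm, n = 100 | Difference, n = 100 per arm | Difference, n = 80 per arm |
|---|---|---|---|
| 0.5 | 0.082 | 0.116 | 0.130 |
| 1 | 0.165 | 0.233 | 0.260 |
| 1.5 | 0.247 | 0.349 | 0.390 |
| 2 | 0.329 | 0.465 | 0.520 |
| 3 | 0.494 | 0.698 | 0.780 |

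The ratio of difference to single arm is √2 = 1.41 whatever the CV. The 80 per arm is the article's completer sample.

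**5. Patient costs.** The questionnaire is described as covering three health-care items. No other instrument in Tables 1 and 2 is described as collecting what patients spend outside health care. The display category therefore has no described source.

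**6. Trimming.** For an assumed log-normal cost, s = √ln(1 + CV²), and the mean after cutting 10% from each tail, divided by the true mean, is [Φ(1.2816 − s) − Φ(−1.2816 − s)] / 0.8. This gives 0.94, 0.82, 0.71, 0.63 and 0.51 at CV 0.5, 1, 1.5, 2 and 3. The shortfall matters only if the trimmed mean is the one used for the conclusion. The article reports both and says that either the usual or the trimmed mean is suitable, without choosing.

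**The case against.** The best defence is that the comparison is there in substance. Utilisation is gathered in both arms, baseline use is held to control group differences, costs are linked to clinical data, the model is to use events reported by participants, and a bootstrap interval is planned. A condensed article need not name an incremental ratio or a net-benefit curve. Varying a proportion in a sensitivity analysis also does not prove that the observed one will be ignored.

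Much of this stands. A reader might infer that the plan discards the randomised comparator or cannot answer the second research question. The documents do not support that, because the data and the baseline control point towards a group comparison. The absence of a named ratio is not the point either.

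What the defence does not meet is that the article is not silent. It gives the economics several detailed paragraphs and states one rule for savings, which treats the two arms differently and rests on an undefined proportion. Condensation does not explain two different model populations.

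Two further readings are tempting and should be resisted:

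- **Travel.** A reader might infer that the plan promises travel costs and then omits them. The table of costs does not name travel; travel savings appear in the abstract's background. The full questionnaire is not shown. The 17 to 84 miles under Location and Setting are distances from outpatient clinics to the medical center, not from patients' homes, so multiplying them by 8 round trips does not give an uncounted cost per patient.
- **Trimming.** A reader might infer that mean cost will be understated. Ordinary means are reported for every component and trimmed means are additional. The stated reason, that payers care about average cost, favours the ordinary mean.

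**Conclusion.** The concern holds in a limited form. The stated rule for savings, the inconsistent model population and the target of the bootstrap interval leave the second primary research question without a committed between-arm estimate of cost and effect. Following the text as written would not use the randomised comparison that the collected data permit.

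The effect on the eventual answer cannot be sized from the article. The one general figure is that an interval for the difference is 1.41 times as wide as that for a single arm, given equal means and variation. At 100 per arm its half-width would be about 12% to 70% of mean cost over assumed CVs of 0.5 to 3. A reader shown only an interval around costs could therefore take the savings estimate to be more precise than it is.

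The missing source for non-healthcare patient costs is a real but smaller mismatch. On trimming, the only open question is which mean decides. This should be corrected, but the trial can still answer its economic question.

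**What to change.** - **Main analysis.** Define it as the observed between-arm difference in arithmetic mean 12-month cost per patient, adjusted for baseline resource use, together with the between-arm difference in response, naming the response measure and time point. Obtain 90% intervals by resampling patients within arm and keeping each patient's cost and response together.
- **Supportive analyses.** Keep the Markov model, the varied Same-Room proportion and the scenarios, labelled as supportive or sensitivity analyses. Define the proportion appropriately treated. Reconcile the model population between Economic Outcome Measures and Economic Analyses.
- **Patient costs.** State a source for non-healthcare costs, for example travel estimated from home-to-clinic distance and recorded attendance, if addresses are available for this use. Otherwise drop the category and state that the analysis takes a health-care perspective.
- **Summary measure.** State that the untrimmed mean drives the conclusion. Trimmed means may stay as an additional display.

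The cost is some extra analyst time. The main analysis needs no new data collection; a travel estimate would need access to addresses, which the article does not list as study data. The Discussion reports 111 participants randomised and only 6 due for Month 12 assessment in October 2008, so at that date the rule could still have been fixed before most 12-month data existed.
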